### Participant eligibility

The following participants are eligible for inclusion:Patients aged ≥ 18 years referred from primary care with symptoms of suspected CRC.Patients with histologically confirmed colorectal adenocarcinoma (stages I-IV) who are treatment naïve (CRC group).

Participants with any of the following will not be eligible for inclusion:i)Previous surgery altering the anatomy of the lower GI tract (e.g., hemicolectomy, anterior resection).ii)Previous treatment (neoadjuvant chemotherapy or radiotherapy or immunotherapy) for CRC.iii)Received bowel preparation for their colonoscopy procedure.iv)History of any other cancer within three years.v)Unable or unwilling to provide informed written consent.

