## Background

In the United Kingdom (UK), colorectal cancer (CRC) is the second most common cause of cancer death, with survival rates amongst the lowest in Europe [1]. If diagnosed early at stage one, the five-year survival is over 90% [2]. However, 23% of patients are diagnosed with advanced disease (stage four) which has a five-year survival of only 10% [3]. Most CRC patients present via the suspected lower gastrointestinal (GI) cancer (30%) or routine (34%) referral pathways, the latter often being associated with significant delay. Twenty-four percent of patients present as an emergency, typically with advanced disease [4].

Early-stage CRC shares many symptoms with common benign conditions and so it can be unclear which patients should be referred for a colonoscopy. Referring all symptomatic patients would overwhelm available resources with demand expected to continue to rise further over the next five years. Annually 1.43 million lower GI endoscopies are performed in the UK, but the diagnostic yield for CRC is lower than 3% [5, 6]. The annual cost of lower Gl endoscopies to the National Health Service (NHS) is estimated to be over £530 million [7]. To improve precision in the early detection of CRC, it is essential to refer patients for colonoscopy who are most likely to have CRC, while not subjecting those at lower risk to an invasive and costly procedure. Therefore, we need sensitive diagnostic tools in primary care that are accurate, easy to perform and accepted by patients.

In the UK, guidelines including the National Institute for Health and Care Excellence (NICE), have recommended the use of the faecal immunochemical test (FIT), which measures the amount of haemoglobin in a stool sample, to triage low-risk symptoms in primary care [8]. Faecal haemoglobin concentrations are known to vary by age, sex, ethnicity, deprivation, cancer stage and iron-deficiency anaemia [9]. Depending on the selected threshold for positivity, sensitivity of FIT for CRC varies between 54 and 93%, specificity between 83 and 95%, with a positive predictive value of 7% in patients with low-risk symptoms [10].

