### COBRA2 study objectives

The objectives of the COBRA2 study are to develop and validate a clinical prediction model (CPM), using an improved technology and methodology, to triage the risk of CRC based on profiles of VOCs obtained from the breath test. The clinical utility of the model for referral for the appropriate reference test will be investigated and compared against the current protocol of referring all patients presenting with symptoms indicative of CRC. We will also perform an exploratory comparison between the breath test and FIT, and assess the performance of combining both tests to detect CRC. This will be followed by a narrow validation study using the same case–control design, to assess the ability of the CPM to distinguish between CRC and non-cancer, and to assess the potential clinical utility of decision rules when used for triaging.

We anticipate an improvement in biomarker identification and quantification due to the use of: (i) updated breath collection device and time-of-flight (TOF) and two-dimensional gas chromatography-mass spectrometry (GC–MS) technology; (ii) calibration curves for target compounds; (iii) avoidance of colonoscopy bowel preparation as a possible confounder, and (iv) additional quality control (QC) steps for biomonitoring thermal desorption (TD) tubes, GC-TOF–MS analysis, and a dedicated laboratory environment, therefore enhancing the lower limits of VOC quantification.

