## Methods

### Study design

COBRA2 is a multicentre, case–control development and validation study. The study involves collection of breath at a single time point from eligible participants and is open to all NHS trusts. The COBRA2 study is sponsored by Imperial College London and has obtained NIHR Clinical Research Network portfolio adoption to support study recruitment. The COBRA2 study commenced in September 2022 and is due to complete by December 2026.

The following groups of participants are being recruited:i)Control group: symptomatic patients who are attending a planned colonoscopy referred under the suspected lower GI cancer pathway. Any patient who is found to have histologically-proven CRC on colonoscopy will be analysed as part of the CRC group.ii)CRC group: patients who either have a confirmed diagnosis of colorectal adenocarcinoma according to a biopsy, or who are due to undergo surgical resection for suspected CRC (with histological confirmation to follow within three months).

The target recruitment for the development of the CPM is 720 patients (470 controls, 250 CRC), aiming for a total of 576 patients (376 controls, 200 CRC) with reliable and complete data (breath test and reference test). For the narrow validation, the target recruitment is up to 250 patients (125 controls, 125 CRC), aiming for 200 patients (100 controls, 100 CRC) with reliable and complete data.

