### Participant enrolment

Participants will be identified from suspected lower GI cancer pathway from NHS trust booking systems (control group) and multidisciplinary team meetings (CRC group) (Fig. 1). Participant eligibility will be confirmed, and participants will be contacted by research staff by telephone at least 24–48 h prior to breath testing. Study details will be provided, including the need to maintain a clear fluid diet for a minimum of 4–6 h prior to testing. The participant information leaflet will be sent to the patient via email or post. Informed consent will be taken by the research staff at the scheduled hospital attendance. Breath sampling will take place at outpatient or pre-assessment clinics for controls and CRC cases prior to any endoscopy or surgery. These in-person endoscopy and surgery pre-assessment appointments are part of patients’ routine care in the study hospitals and therefore patients usually do not need to make additional visits to the hospital for testing. Neither groups will have had bowel preparation prior to their research visit. Using a structured proforma to allow integration of symptoms in the diagnostic model, patient demographics, co-morbidities, medication history, symptoms, cancer characteristics and FIT results are being recorded from either primary or secondary care records (Supplementary material Table S1).

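### CRC cases need not be symptomatic or referred from primary care although every control is, so sensitivity, symptom weights and triage utility may be biased for the intended symptomatic use

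*Protocol article*

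**What the plan says.** All references are to the protocol article.

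- **Controls.** Study design defines them as "symptomatic patients who are attending a planned colonoscopy referred under the suspected lower GI cancer pathway".
- **Cases.** The same section defines them as "patients who either have a confirmed diagnosis of colorectal adenocarcinoma according to a biopsy, or who are due to undergo surgical resection for suspected CRC". In the second situation histology comes afterwards. Neither symptoms nor route is mentioned.
- **Eligibility.** Participant eligibility lists two inclusion criteria. One, without a group label, covers adults "referred from primary care with symptoms of suspected CRC". The other is labelled for the cases: "Patients with histologically confirmed colorectal adenocarcinoma (stages I-IV) who are treatment naïve (CRC group".
- **Source.** Participant enrolment identifies people from the "suspected lower GI cancer pathway from NHS trust booking systems (control group) and multidisciplinary team meetings (CRC group".
- **Overlap.** Study design adds: "Any patient who is found to have histologically-proven CRC on colonoscopy will be analysed as part of the CRC group".
- **Intended use.** COBRA2 study objectives says the model's clinical utility for referral will be "compared against the current protocol of referring all patients presenting with symptoms indicative of CRC".
- **Model inputs.** Participant enrolment says symptoms are recorded so that they can be built into the model. Statistical analysis adds patient and clinical characteristics to the breath test in the final models.
- **Routes to diagnosis.** Background states: "Most CRC patients present via the suspected lower gastrointestinal (GI) cancer (30%) or routine (34%) referral pathways". It puts emergency presentation at 24%, typically with advanced disease.

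**The concern.** Case-control sampling is a legitimate economy when the disease is rare, but it gives the right sensitivity only if the cases resemble those the test will meet. Here the test is meant for people who present with symptoms. Controls must be such people and cases need not be.

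Two things are at stake. First, sensitivity, on which the study is powered, is averaged over cases that may include people whom a symptomatic triage rule would never see, and the cut-off is chosen on the same mix. Second, if symptoms are predictors, their coefficients compare a group selected for having symptoms with one that was not. That pulls the coefficients down by an amount set by recruitment rather than by disease.

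The narrow validation uses the same case-control design, so it would reproduce either bias and appear to confirm the model.

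**Working it through.** **1. The two groups side by side**

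| | Controls | CRC cases |
|---|---|---|
| Symptoms | required | not mentioned |
| Route | suspected lower GI cancer pathway | not mentioned |
| Found through | booking systems | multidisciplinary team meetings |
| Defined by | planned colonoscopy | histology or planned resection; treatment naïve |

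**2. Cases that share the controls' route by design.** Statistical analysis gives a CRC risk of about 5–7% on the pathway. Among 470 control-stream recruits that is 470 × 0.05 = 23.5 to 470 × 0.07 = 32.9 cancers, or 9–13% of 250 cases. If 470 non-cancer controls must remain, it is 470/0.95 − 470 = 24.7 to 470/0.93 − 470 = 35.4, or 10–14%. The other 86–91% of cases come through a stream with no stated route condition.

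**3. Possible route mix in that stream (Background figures).** Suspected-cancer plus routine referral: 30 + 34 = 64%. Remainder: 100 − 30 − 34 − 24 = 12%, route not named. With emergencies left out: 64/76 = 84%. Of 200 analysable cases, 128 or 168 would be referred. This assumes that study cases follow the national mix and that both referral routes count as symptomatic primary-care referral. The article states neither.

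**4. The plan's own figure, then the referred subset.** One-sample arcsine test, h = 2·asin√0.90 − 2·asin√0.83 = 0.206, one-sided α = 0.05, power = Φ(h√n − 1.645).

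- n = 200: 89.9%. The stated 90% is reproduced.
- n = 128: 76%.
- n = 168: 85%.

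In the narrow validation, 100 analysable cases would give 64 or 84 referred cases. The standard error √(p(1−p)/n) at sensitivity 90% to 85% is 3.8–4.5% with 64 and 3.3–3.9% with 84. Both stay within the 5% upper end that Sample size accepts.

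**5. Case mix and sensitivity (illustration).** At a fixed cut-off, overall sensitivity = s × referred + (1 − s) × other, where s is the referred share. Take overall sensitivity at the target 90%.

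- If referred cases are detected 10 points less often than the others, referred sensitivity is 0.90 − 0.36 × 0.10 = 86.4% at s = 64%, or 0.90 − 0.16 × 0.10 = 88.4% at s = 84%.
- The lowest possible value, with every other case detected, is (0.90 − 0.36)/0.64 = 84.4%, or (0.90 − 0.158)/0.842 = 88.1%.

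The 10-point gap is an assumption. If the other cases are harder to detect, the bias runs the opposite way.

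**6. Symptom coefficients (illustration).** Assume a symptom present in 60% of controls, and a share a of cases with no symptoms. Crude OR = [p(1−a)/(1−p(1−a))]/(0.6/0.4), with p = 0.60 for a true OR of 1.0 and p = 0.75 for a true OR of 2.0.

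| a | true OR 1.0 appears as | true OR 2.0 appears as |
|---|---|---|
| 0% | 1.00 | 2.00 |
| 12% | 0.75 | 1.29 |
| 20% | 0.62 | 1.00 |

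The direction follows from the design. The values of a and the 60% are assumed.

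**The case against.** The strongest reply is that COBRA2 claims little. COBRA2 study objectives speaks only of potential utility in the narrow validation. The Abstract says that broad validation in unselected symptomatic patients is required, and Discussion plans COBRA3 with re-calibration. A reader might infer that the design cannot answer the triage question at all; the documents do not support that, given these limits. The reply still leaves the point standing. COBRA3 comes after predictors, coefficients and cut-off have been chosen, and re-calibration to prevalence corrects neither coefficients nor case mix.

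The unlabelled criterion may also have been meant for everyone. It holds the only age limit, and reading the two criteria as strict alternatives would leave cases with no minimum age. That is a fair point about wording, but the group definitions in Study design and the separate case criterion favour the other reading. Either way the text needs settling.

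Three further readings go too far:

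- **That about 70% of cases are mismatched.** This counts the 34% of routine referrals as unsuitable. It also ignores that participants are telephoned at least 24–48 h ahead and sampled at outpatient or pre-assessment clinics, which makes emergencies less likely.
- **That the model has learned the route to diagnosis.** This is a plausible inference only. Nothing in the article links VOCs to route, and symptom weights do not touch the breath-only model, which is developed first.
- **That a real symptom effect would vanish.** This happens in the table only because 0.75 × 0.80 equals the assumed 60%. The article does not say that the 12% by unnamed routes lack symptoms.

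**Conclusion.** The point holds in a limited form. As written, cases need not be symptomatic or referred, and controls must be both. The resulting sensitivity, symptom coefficients and utility may therefore be biased for symptomatic triage, and the article does not name this as a limitation.

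The size cannot be computed from the article, because it states neither the route mix among enrolled cases nor how detection differs by route. If cases follow the Background figures, between about 16% (emergencies absent) and 36% come by routes other than suspected-cancer or routine referral. The shift in sensitivity is then bounded as in step 5, at a fixed cut-off and an overall value of 90%. Those bounds do not cover distortion of coefficients or of predictor selection.

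This is an inexpensive improvement worth making. It is not a reason to reject the design.

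**What to change.** 1. In Study design and Participant eligibility, state whether the symptomatic primary-care referral criterion applies to CRC cases.
2. Record route to diagnosis and presenting symptoms for every case from existing records.
3. In development and in narrow validation, report sensitivity, performance at the cut-off and clinical utility in symptomatic referred cases alongside the all-case estimate. Tie the triage-utility claims to the former.
4. Estimate symptom coefficients only with symptomatic referred cases, or leave symptoms out of the model fitted to cases from all routes.

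The cost is one data field at most. Supplementary Table S1 is not at hand, so route may already be collected. The estimate in referred cases is less precise: 76–85% power with 128–168 cases, against the stated 90%. Recruitment began in September 2022, so restricting the main case set outright would be a real trade-off. Reporting both estimates avoids it and discards no enrolled case.

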### Sample size

We have powered our study on sensitivity given the poor prognosis of CRC and the clinical importance of minimising missed diagnoses. The sample size calculation aimed to estimate sensitivity and specificity to acceptable precision using a one-sided Binomial test against a fixed target sensitivity. This was implemented using the R package pwr [26]. Sample size was explored for target sensitivities of 85% to 95% and specificities of 80% to 90%, based on the results from the COBRA1 study. For a target sensitivity of 90%, a sample of 200 CRC cases yields 90% power for the lower (one-sided) 95% confidence interval (CI) limit to be ≥ 83%. For a target specificity of 85%, based on the published specificity for FIT at 10 µg/g, a sample size of 262 controls provides 90% power for the lower limit of the 95% CI to be ≥ 78%. Additional controls (total 376) are included to allow assessment of heterogeneity. Reliable and complete data is therefore required in 576 patients (376 controls, 200 CRC). To account for 20% attrition (e.g., incomplete colonoscopy or breath data), we will recruit a total of 720 patients (470 controls and 250 CRC cases) for CPM development. This sample size allows us to estimate the AUROC with a standard error of less than 2% provided it is at least 0.8, and provides acceptable power for estimating other performance measures. Sample size estimation is consistent with methods suggested by Riley et al. [27] for development of diagnostic models. In the narrow validation study, we aim to recruit an equal number of CRC cases and controls, and similarly allow for a 20% attrition rate. The calculated sample size of up to 250 patients (125 controls, 125 CRC), based on the target sensitivity and specificity (85% to 90%), will ensure sufficient precision in estimating diagnostic accuracy (standard errors for sensitivity and specificity 3.5% to 5%), discrimination (standard error for AUROC < 3%), and calibration (standard error for observed/expected cases < 7.5%), whilst maintaining feasibility [28].

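### The validation standard errors for sensitivity and specificity, given as 3.5% to 5%, should be 3.0% to 3.6% on the protocol's own inputs

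*Protocol article*

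**What the plan says.** The Study design section sets the validation target, "aiming for 200 patients (100 controls, 100 CRC) with reliable and complete data". The Sample size section gives the recruitment figure, "The calculated sample size of up to 250 patients (125 controls, 125 CRC"), and says that the study will "similarly allow for a 20% attrition rate". The two agree: 125 × 0.80 = 100 per group.

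The Sample size section then says that the calculation is "based on the target sensitivity and specificity (85% to 90" per cent) and lists the precision that follows:

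- for sensitivity and specificity, "standard errors for sensitivity and specificity 3.5% to 5" per cent;
- for discrimination, "standard error for AUROC < 3" per cent;
- for calibration, a standard error of the observed/expected ratio below 7.5%.

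The Discussion repeats, without figures, that the validation will be precise enough.

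**The concern.** The standard error of a sensitivity or specificity depends only on the proportion and on the number of cases or controls. The protocol gives both, so the range can be checked directly. It does not match: only its lower end is close to a value the design produces, and the rest, up to 5%, lies above anything that 100 per group gives at 85% to 90%.

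What is at stake is the stated justification for the validation sample. A reader who takes 5% at face value expects a 95% confidence interval of about ±9.8 percentage points (1.96 × 5%). The design gives about ±5.9 to ±7.0 points. A reader may also wonder whether the figure comes from a different sample size from the one planned.

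**Working it through.** **Inputs.** Complete data in 100 cases and 100 controls (Study design); 125 recruited per group, 20% attrition, sensitivity and specificity of 85% to 90%, and the three stated precision figures (all Sample size).

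**1. Standard error of a proportion.** SE = √(p(1 − p)/n).

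| n per group | p = 0.85 | p = 0.90 |
|---|---|---|
| 100 (complete data) | √(0.1275/100) = 3.57% | √(0.09/100) = 3.00% |
| 125 (all recruited) | √(0.1275/125) = 3.19% | √(0.09/125) = 2.68% |

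The stated 3.5% to 5% is not reproduced. On the planned complete data the range is 3.0% to 3.6%.

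**2. What a standard error of 5% would imply.** n = p(1 − p)/SE².

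- At 85%: 0.1275/0.0025 = 51 per group.
- At 90%: 0.09/0.0025 = 36 per group.

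Both are about half the planned number or less. Even with 80 per group, the larger standard error (at 85%) is 3.99%.

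**3. Do the other figures in that sentence fit 100 per group?**

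*Observed/expected ratio.* With case fraction φ = 0.5 and N patients in total, SE = √((1 − φ)/(Nφ)) = √(1/N).

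- N = 200: 7.07%, which meets the limit of 7.5%.
- N = 102 (51 per group): 9.90%, which does not.
- N = 72 (36 per group): 11.79%, which does not.

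The 7.5% limit needs N of at least 1/0.075² = 177.8, so 89 per group. There the sensitivity standard error at 85% is 3.78%, still well short of 5%.

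*AUROC.* The protocol does not give the AUROC it assumed for validation, so I use the Hanley–McNeil formula over a range.

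| AUROC | 100 per group | 51 per group | 36 per group |
|---|---|---|---|
| 0.85 | 2.75% | 3.87% | 4.61% |
| 0.90 | 2.26% | 3.18% | 3.80% |
| 0.91 (the COBRA1 value) | 2.15% | 3.02% | 3.61% |

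The limit of 3% is met at 100 per group throughout this range and missed at 51 and 36, though at 51 per group with an AUROC of 0.91 only just. The observed/expected ratio is the firmer check, because it needs no assumed AUROC.

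The two neighbouring figures therefore fit 100 per group. The sensitivity and specificity figure is the one out of line.

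**4. The development power figures, for comparison.** The section names the R package pwr, which uses the arcsine effect size h = 2·asin√p₁ − 2·asin√p₀, with n = ((1.645 + 1.282)/h)².

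- Sensitivity 0.90 against 0.83: h = 0.2065, n = 200.9, power at 200 = 89.9%.
- Specificity 0.85 against 0.78: h = 0.1810, n = 261.4, power at 262 = 90.1%.

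Both stated figures are reproduced.

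**The case against.** **The range might run from target to worst case.** At 100 per group, the binomial standard error is 3.57% at p = 0.85 and reaches its maximum of exactly 5.0% at p = 0.5. On that reading, 3.5% to 5% needs no other sample size. This is a plausible origin, and it is why the fix offers the authors the choice of stating other proportions. It does not make the sentence right as printed, because the sentence ties the figures to 85% to 90% and never mentions a worst case.

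**The wording "up to" 250 might allow a smaller sample.** The observed/expected limit in the same sentence rules out fewer than 89 per group, and at 89 the standard error is still below 4%.

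**The error is harmless.** It is conservative, and no sample size, analysis or decision rule depends on it. That stands, and it limits the point to a correction of the text.

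**A stronger reading: the development power is wrong too.** The section describes "using a one-sided Binomial test against a fixed target sensitivity" and says that "a sample of 200 CRC cases yields 90% power for the lower (one-sided) 95% confidence interval (CI) limit to be ≥ 83" per cent. A reader might take this as an exact test. With 200 cases, an exact test needs at least 176 detections (175 gives one-sided p = 0.0507) and has 85.5% power, so the 90% would look overstated. The protocol does not support that inference. It specifies neither an exact test nor an exact limit, and the software it names reproduces the 90%. Wilson and Jeffreys limits also give 90.0%. The exact result is largely discreteness: with 201 cases the cut-off stays at 176 and the power is 89.5%. The choice of interval can be left to the analysis plan.

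**Conclusion.** The validation standard errors for sensitivity and specificity are wrong as written. On the protocol's own inputs they are 3.0% (at 90%) to 3.6% (at 85%), not 3.5% to 5%. The stated upper end is 5/3.57 = 1.4 times the largest value the design produces.

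This assumes simple binomial sampling in each group, 100 per group with complete data, and true values of 85% to 90%. It does not depend on whether the 100 complete or the 125 recruited per group are used: at 125 the values are smaller still.

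The consequence is small. Precision is better than promised, the planned validation size remains justified, and the AUROC and observed/expected figures beside it are consistent with that size. The 90% power figures for 200 cases and 262 controls stand.

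**What to change.** In the Sample size section, restate the validation standard errors for sensitivity and specificity as 3.0% to 3.6%, for 100 per group with complete data and true values of 90% down to 85%. If the authors meant the range to cover other proportions, for example a worst case, they should keep 3.5% to 5% and name those proportions in place of 85% to 90%.

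The cost is one edited line. Recruitment, analysis and the development power statement do not change.

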### Statistical analysis

The COBRA2 study is a development and narrow validation study which follows the validation strategy described by Cowley et al. [30] and Transparent Reporting of a multivariable prediction model for Individual Prognosis Or Diagnosis (TRIPOD) guidelines [31]. This method ensures the development of a rigorous and robust CPM that maximises the potential benefit on patient care and decision-making in clinical practice. For development and validation, we use a case–control design for efficiency given that CRC has a low prevalence in the population. Patients referred on the suspected lower GI cancer pathway have a CRC risk of approximately 5–7% [32]. We will use statistical methods for model development and validation. Initially, we will confirm previously identified VOCs using enhanced measurement methods. Using VOCs from COBRA1 as a base, a screening step will identify the most promising additional predictors. Then logistic regression methods will be used to develop a model based on the breath test alone, including all identified VOCs. To reduce over-fitting, we will use model reduction methods such as the elastic net, least absolute shrinkage and selection operator (LASSO) or Harrell’s stepdown approach [33]. For internal model validation, the following will be used [33, 34]:10-fold cross-validation and median values of the performance measures across folds.For calibration, predicted risks of CRC will be plotted against the observed risks.For overall predictive performance Mean Absolute Prediction Error will be estimated (0%: perfect prediction, 100%: no predictive value).For discrimination, the non-parametric AUROC will be calculated, and the threshold that achieves the best trade-off between sensitivity and specificity will be extracted.

For final models, we will use logistic regression modelling to also include patient and clinical characteristics. We will assess linearity of relationships between CRC risk and continuous variables, and explore categorical variables and two-way interactions, including interactions with the breath test. All candidate predictors will initially be entered into the model, before simplification based on Wald statistics (significance < 0.05), size of the predictive weight (odds ratio) and clinical opinion. If there are missing patient or clinical characteristics, we will consider using imputation techniques [35].

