## Discussion

The COBRA2 study aims to develop and validate the CPM for the detection of CRC based on a breath test. The narrow validation will ensure sufficient precision in estimating diagnostic accuracy, discrimination, and calibration whilst maintaining feasibility. The case–control design of symptomatic and confirmed CRC patients has been chosen for COBRA2 to efficiently establish a CRC detection model with a robust reference standard for breath and an enriched cancer population. A large-scale triple-blind broad validation study (COBRA3) will follow in patients where the diagnosis is unknown. Persons collecting breath, carrying out VOC analysis and classifying into cancer/no-cancer will all be unaware of diagnosis. The test will be re-calibrated to reflect CRC prevalence in the broad validation population. A detailed economic analysis will also be performed to fully assess different decision rules from a patient and policy viewpoint.

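### The model is developed at a planned 34.7% CRC and its observed/expected calibration is assessed at a planned 50% CRC; without a stated adjustment, O/E is expected to exceed 1 by design

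*Protocol article*

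**What the plan says.** Under Study design, the development target is given as "aiming for a total of 576 patients (376 controls, 200 CRC) with reliable and complete data", and the narrow validation target as "aiming for 200 patients (100 controls, 100 CRC) with reliable and complete data". The Sample size section confirms the validation ratio: "we aim to recruit an equal number of CRC cases and controls".

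The same section lists the quantities that the narrow validation should estimate precisely. One of them is "calibration (standard error for observed/expected cases < 7.5" per cent.

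On modelling, the Statistical analysis section says: "Then logistic regression methods will be used to develop a model based on the breath test alone". The calibration plot described there comes under internal validation, where the case fraction is the same as in model fitting.

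The only statement on adjusting for prevalence is in the Discussion, about the future broad validation study, COBRA3: "The test will be re-calibrated to reflect CRC prevalence in the broad validation population". The article describes no offset, weighting or re-calibration between the development and narrow validation samples.

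**The concern.** In a case-control sample the logistic intercept absorbs the sampling ratio. The predicted risks are therefore risks for a population with the development sample's share of cancers. Applied unchanged to a sample with a larger share, they add up to too few cases even if every VOC coefficient is right.

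O/E is read against 1, and here 1 is not the value that a sound model would produce. Two errors of interpretation could follow:

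- Apparent under-prediction could be put down to the model when the recruitment ratios cause it.
- A model that over-predicts by a similar amount could return an O/E near 1 and be reported as well calibrated.

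A calibration intercept or calibration plot in the narrow validation would be shifted in the same way.

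**Working it through.** **Inputs from the article.** Development: 200 CRC, 376 controls (Study design). Validation: 100 CRC, 100 controls (Study design). Target SE of O/E: below 7.5% (Sample size). COBRA1 AUROC: 0.91 (Background). AUROCs from 0.80 to 0.95 are shown as an assumed range.

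**Step 1. Case fractions.** Development: 200/576 = 34.7%; the recruitment targets give the same, 250/720 = 34.7%. Validation: 100/200 = 50%.

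**Step 2. Reproduce the article's precision figure.** The usual formula is SE(ln O/E) = √[(1 − φ)/(nφ)], where φ is the case fraction.
- n = 200, φ = 0.50: √(0.50/100) = 0.0707, which meets the target.
- n = 200, φ = 0.347: 0.0970, which does not.

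So the stated figure is reproducible, and at 200 evaluable patients it fits an O/E assessed in the 50% sample.

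**Step 3. Shift in log-odds between the samples.** logit(0.50) − logit(0.347) = 0 − ln(200/376) = ln(1.88) = 0.631.

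**Step 4. Expected O/E without adjustment.** Assume a score x distributed N(0,1) in controls and N(d,1) in cases, with d = √2·Φ⁻¹(AUROC). The model perfectly calibrated to the development mix is p(x) = expit[ln(200/376) + d·x − d²/2]. Its mean prediction over the development mix is 0.347, as it should be. For validation, average p(x) over cases and controls at 50:50 and multiply by 200. The observed count is 100. The last column comes from 20,000 simulated validations, with the interval built from the SE of 0.0707.

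| AUROC | Expected cases | O/E | ln(O/E) ÷ 0.0707 | 95% interval excludes 1 |
|---|---|---|---|---|
| 0.80 | 77.3 | 1.29 | 3.6 | 99.9% |
| 0.85 | 80.3 | 1.25 | 3.1 | 98% |
| 0.90 | 84.0 | 1.19 | 2.5 | 81% |
| 0.91 | 84.8 | 1.18 | 2.3 | 74% |
| 0.95 | 88.9 | 1.13 | 1.7 | 29% |

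The upper limit, with no discrimination, is 0.50/0.347 = 1.44.

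**Step 5. With adjustment.** Adding 0.631 to the linear predictor gives an expected O/E of 1.00 at every AUROC tried.

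**Step 6. Masking.** An intercept that is too high by 0.631 for the development mix would be exactly cancelled by the change of ratio, and the unadjusted O/E would be centred on 1.

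**A note on the SE.** The 1:1 design fixes the observed count, so the binomial SE overstates the real variation. The simulated SD of ln(O/E) was about 0.04 at AUROCs from 0.80 to 0.95. Measured against that, the shift is larger than the table suggests.

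**The case against.** The strongest reply is that this is a condensed article. It gives a precision target for O/E but does not say how expected cases will be computed, and an intercept offset is ordinary analysis-plan detail. The authors clearly know that prevalence matters: they contrast the case-control mix with a 5–7% risk on the referral pathway and commit to re-calibration in COBRA3. That commitment does not exclude an offset in the narrow validation. This part stands, so the point has to be conditional: the shift arises if the development intercept is carried over unchanged.

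The reply does not dispose of the point. The article itself fixes both ratios, names the measure, sizes the validation on it, and places prevalence re-calibration only in the next study. The COBRA3 step does not make O/E interpretable in the narrow validation.

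A reader might infer more: that the plan specifies an invalid analysis, that a sound model is bound to be judged miscalibrated, or that it could be rejected as a result. The article does not support these readings:

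- No computation of expected cases is written down.
- No decision is tied to O/E. The COBRA2 study objectives describe the narrow validation as assessing discrimination and the potential utility of decision rules, and the study is powered on sensitivity.
- At AUROC 0.95 the interval would exclude 1 in only about 29% of validations, and the article expects better biomarker measurement than in COBRA1.
- O/E would reflect both the model and the recruitment ratios, not the ratios alone.

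**Conclusion.** The concern holds in conditional form. At the planned numbers, carrying the development intercept over unchanged gives an expected O/E of about 1.13 to 1.29 for a model calibrated to the development mix, across AUROC 0.95 to 0.80, and 1.18 at the COBRA1 value. The direction follows from the two ratios for any imperfect model.

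The size rests on three things: the equal-variance binormal score, the AUROC reached, and the achieved counts. Those counts may differ from target, because controls found to have CRC move to the CRC group and the validation sample is a maximum. The stated SE is not wrong; what lacks meaning without an adjustment is the reference value of 1.

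AUROC is unaffected, as are sensitivity and specificity at a threshold carried over on the same scale. This is a moderate point about a secondary performance measure, and the primary accuracy results do not depend on it.

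**What to change.** State, before the validation data are analysed, that O/E, the calibration intercept and the calibration plot in the narrow validation will be computed after adding logit(validation case fraction) − logit(development case fraction) to the linear predictor. Use the achieved counts; at target numbers the offset is about +0.63. Weighting both samples to one common prevalence is an alternative. Add that uncorrected O/E is not interpretable against 1. Use the offset for calibration only, and keep the classification threshold on the development scale so that sensitivity and specificity are unchanged.

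Matching the validation ratio to development would also remove the shift, but at 200 evaluable patients the SE would rise to 9.7% and miss the stated target.

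The offset costs a sentence or two of text and a line of code, with no extra patients. If the analysis plan already contains such an offset, a cross-reference closes the point.
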